
3.2. Research Hypotheses and Expected Results

Our hypothesis is that combining continuous IV lidocaine infusion with epidural anesthesia during management of a major abdominal surgery does not increase the plasma concentrations of local anesthetics beyond toxic thresholds. Through repeated blood sampling, we hope to show that plasma levels of the local anesthetics remain well below toxic values. Furthermore, by observing an absence of adverse events related to local anesthetic use (central nervous system effects – which are rare – such as seizures, dizziness, loss of consciousness, paresthesia, tongue numbness, hyperacusis, tinnitus, visual disturbances, dysarthria, muscle tremors; hypoesthesia; and cardiac effects such as bradycardia, tachycardia, conduction disturbances up to cardiac arrest), we hope to demonstrate no cumulative cardiac or neurological toxicity when both are used together.

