3.3. Rationale for Methodological Choices

Lidocaine and ropivacaine are both metabolized in the liver. The toxic thresholds for these two local anesthetics are becoming well known: for lidocaine, the therapeutic plasma range is 1.4 to 5 µg/mL, and toxicity can begin at concentrations above 5 µg/mL. Neurotoxic effects appear around 15 µg/mL and cardiotoxicity around 21 µg/mL. For ropivacaine, the usual maximal total venous concentration not to exceed is about 2.2 µg/mL. The half-life of IV lidocaine is 80–110 minutes. Ropivacaine, when administered into the epidural space, is absorbed completely in a biphasic manner, with half-lives of approximately 14 minutes and 4 hours for the two phases in adults. Its slow absorption is the rate-limiting step in its elimination, leading to a longer apparent elimination half-life after epidural administration compared to IV administration. In our study, five plasma measurements of lidocaine and ropivacaine will be taken at different times during surgery and up to 24 hours post-op: lidocaine level at 30 minutes after the bolus, lidocaine level at the end of its infusion (i.e. at surgical closure), lidocaine level at 2 hours after starting the epidural, ropivacaine level at 2 hours after starting the epidural, and ropivacaine level at 24 hours after starting the epidural. Achieving a steady plasma level during a continuous infusion takes more than 60 minutes, which is why an initial bolus is recommended. Given the rapid distribution after a bolus, it’s recommended to start the maintenance continuous infusion promptly if a stable plasma concentration is to be maintained for infusions longer than 20 minutes. This justifies our first blood draw at 30 minutes after the lidocaine bolus. Thereafter, the plasma concentration remains stable around a level determined by the dose and infusion rate, which is why we will measure at the moment of stopping the infusion to capture the intraoperative plasma level of lidocaine. For the epidural, systemic absorption is gradual. Studies show a linear increase in plasma levels during the continuous infusion; the 2-hour ropivacaine level will provide an initial indication of ropivacaineemia. The lidocaine sample taken at the same 2-hour mark will indicate the residual lidocaine concentration at the time ropivacaine levels are rising, giving insight into the overlap period of both local anesthetics, and whether lidocaine’s decline follows the expected pattern when another local anesthetic is present. Finally, the ropivacaine level at 24 hours post-epidural induction will reflect the average plasma concentration after a full day of continuous epidural ropivacaine infusion. Lidocaine is not measured at 24h because it will have been fully eliminated by that time.

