5. ENDPOINTS

5.1. Primary Endpoint

The primary endpoint is the plasma concentration of ropivacaine and lidocaine falling outside the safe range at the various time points of patient management. We will obtain five plasma measurements of lidocaine and ropivacaine at different times during surgery and up to 24 hours postoperatively: lidocaine level at 30 minutes after the bolus injection, lidocaine level at the end of its infusion (i.e. at surgical closure), lidocaine level at 2 hours after induction of the epidural, ropivacaine level at 2 hours after induction of the epidural, and ropivacaine level at 24 hours after induction of the epidural. The toxic thresholds of these two local anesthetics are known: for lidocaine, the safe plasma range is 1.4 to 6 µg/mL; neurotoxicity appears from 15 µg/mL and cardiotoxicity from 21 µg/mL. For ropivacaine, the usual maximum total venous concentration not to exceed is around 2.2 µg/mL. Any single measurement above the toxicity threshold will be considered an occurrence of toxicity.

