12.2. Statistical Methods

Quantitative variables will be described as mean ± standard deviation and median [range]. Qualitative variables will be described as percentages with 95% confidence intervals

Primary endpoint analysis: We will calculate the percentage of patients who have at least one plasma concentration of ropivacaine or lidocaine outside the safe range. A 95% confidence interval (using an asymptotic or exact method as appropriate) will be computed for this percentage.

Secondary endpoint analysis: The percentage of patients experiencing a toxic event will be calculated with a 95% confidence interval (asymptotic or exact method). All statistical analysis will be performed using SAS software version 9.4

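### The primary event is defined two ways: read literally, the analysis counts lidocaine below 1.4 µg/mL, including normal washout at 2 h, as a safety failure

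*Protocol*

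**What the plan says.** **Analysis rule.** Section 12.2 states: "We will calculate the percentage of patients who have at least one plasma concentration of ropivacaine or lidocaine outside the safe range". It names no direction and exempts no sample. Section 12.1 plans on the same quantity, at about 10%, with 50 patients.

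**Range.** Section 5.1 says "for lidocaine, the safe plasma range is 1.4 to 6 µg/mL", and the summary in section 1 gives the same limits. For ropivacaine only a maximum is given, about 2.2 µg/mL, so the question of direction concerns lidocaine alone.

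**Competing rule.** Section 5.1 ends: "Any single measurement above the toxicity threshold will be considered an occurrence of toxicity". The hypothesis in section 3.2 is that the combination "does not increase the plasma concentrations of local anesthetics beyond toxic thresholds", and the aim in section 3.1.2 is likewise that toxic levels are not reached.

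**Status of 1.4 µg/mL.** Section 3.3 says "for lidocaine, the therapeutic plasma range is 1.4 to 5 µg/mL, and toxicity can begin at concentrations above 5 µg/mL". There, 1.4 is the floor of a therapeutic range, and the upper limit is 5, not 6.

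**The 2 h sample.** Lidocaine stops when the epidural starts (sections 1 and 6.1), so the third lidocaine sample falls 120 min after stopping. Its purpose is given in section 3.3: "The lidocaine sample taken at the same 2-hour mark will indicate the residual lidocaine concentration". The same section states: "The half-life of IV lidocaine is 80–110 minutes".

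**The concern.** A lower limit taken from a therapeutic range says nothing about toxicity. If it stays in the primary event, a patient whose lidocaine was never high, and who cleared it as expected, counts the same as a patient whose level was too high. The design includes a sample taken in order to observe that decline, so low values there are expected.

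This percentage is the only primary result of a single-arm study meant to support the safety of the combination and the standardisation of practice. The two rules in the protocol could give very different percentages from identical data. If the choice stays open until the levels are known, it can be made with the answer in view.

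**Working it through.** **1. The plan's own precision figures (section 12.1).** 95% Wald half-width = 1.96 × √(p(1−p)/50).
- p = 0.10: 8.3%, against the stated ±8%.
- p = 0.50: 13.9%, against the stated ±14%.

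Both reproduce to rounding.

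**2. Washout at the 2 h sample.** Inputs: 120 min since stopping; half-life 80 to 110 min (section 3.3); lower limit 1.4 µg/mL (section 5.1). Fraction remaining = 2^(−120/half-life). Level needed at stopping = 1.4 / fraction.

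| Half-life | Fraction left | Level needed at stopping to be at or above 1.4 at 2 h |
|---|---|---|
| 80 min | 2^(−1.5) = 0.354 | 1.4/0.354 = 3.96 µg/mL |
| 110 min | 2^(−1.09) = 0.469 | 1.4/0.469 = 2.98 µg/mL |

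A patient who stops at 2.5 µg/mL, inside the range, falls to 0.88–1.17 µg/mL and becomes a primary event under the literal rule.

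**3. Share of patients flagged by this sample alone.** The protocol gives no end-of-infusion level, so these are assumptions.

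*Uniform over the documents' ranges:* share = (level needed − 1.4)/(upper limit − 1.4).
- 1.4–6 µg/mL: (2.98 − 1.4)/4.6 = 34% to (3.96 − 1.4)/4.6 = 56%.
- 1.4–5 µg/mL: (2.98 − 1.4)/3.6 = 44% to (3.96 − 1.4)/3.6 = 71%.

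*Log-normal, CV 30%:* share = Φ(ln(level needed/GM)/σ), with σ = √ln(1 + 0.3²) = 0.294.

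| Geometric mean at stopping (µg/mL) | Half-life 110 min | Half-life 80 min |
|---|---|---|
| 2.0 | 91% | 99% |
| 2.5 | 73% | 94% |
| 3.0 | 49% | 83% |
| 4.0 | 16% | 49% |

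**4. Timing in the visit table.** Section 10.2 places this sample 2 h after surgery. With the infusion stopped about 30 min before the end of surgery, that is about 150 min after stopping. The fraction left is then 27% to 39% and the level needed 5.14 to 3.60 µg/mL, so more patients would be flagged.

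**5. Effect of the two rules on one data set.** Suppose no patient of 50 exceeds an upper limit. Under the upper-side rule the result is 0/50, with an exact 95% upper limit of 7.1%. Under the literal rule, with the uniform assumption, 34% to 71% of 50 is about 17 to 36 patients. The Wald half-width at those proportions is about 13% to 14%, still within the stated worst case.

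**The case against.** The strongest reply is that the two-sided reading is not settled. Section 12.2 states no direction, section 5.1 closes with an upper-side rule, the aim and hypothesis concern toxic thresholds only, and a planned proportion near 10% fits an upper-side event. This stands, and it is why the defect is an inconsistent definition rather than a fixed analysis known to fail. It does not remove the defect: the range attached to the endpoint has a lower limit, and the only analysis rule counts values outside that range.

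Three stronger readings are tempting but not supported:

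- *That most patients will be flagged.* This depends on end-of-infusion levels, which the protocol does not give. At a geometric mean of 4.0 µg/mL the assumed share is 16% to 49%.
- *That the 10% assumption cannot hold.* It can in a narrow case. With a 110 min half-life, a geometric mean of 4.2 µg/mL and a CV of 20% (all assumed except the half-life), about 4% fall below 2.98 at stopping and about 4% exceed 6, roughly 8% in total.
- *That low values would contradict the hypothesis.* They cannot, because the hypothesis concerns exceeding toxic thresholds. The study is descriptive, with no test or success criterion attached to the percentage.

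It is also fair to say that section 12.2 plans means, medians and ranges for quantitative variables, so high concentrations would remain visible, and that clinical toxicity is analysed separately as the secondary endpoint. Those limit the damage but do not correct the headline figure.

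**Conclusion.** The point holds as a contradiction within the protocol over whether lidocaine below 1.4 µg/mL is a primary event. Under the literal rule, a large share of patients, possibly most, would be counted because of normal elimination. The washout cut-offs of 2.98 and 3.96 µg/mL follow from the protocol's own half-life, assuming single-exponential decline. The shares, 34% to 71% under the uniform assumption and 16% to 99% across the log-normal cases, rest on assumed end-of-infusion levels and are only as firm as those assumptions. All exceed the planned 10%, which is unlikely to hold under that rule.

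The planned size and its worst-case precision survive. What is damaged is interpretation: a safety percentage that mixes elimination with toxicity. Because the protocol itself fixes the primary event, and does so inconsistently, this should be settled before any levels are analysed.

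**What to change.** - In the summary and in sections 5.1, 12.1 and 12.2, define the primary event identically, as at least one lidocaine or ropivacaine value above its stated upper limit.
- Remove the 1.4 µg/mL lower bound from the event. Report values below it descriptively, for the two samples governed by the infusion (30 min after the bolus and at stopping).
- Tabulate exceedances by drug and by time point.
- Reconcile the lidocaine upper limit, which is 6 µg/mL in the summary and section 5.1 but 5 µg/mL in section 3.3. Also state which figure the toxicity threshold in section 5.1 refers to, since that section lists 15 and 21 µg/mL as well. Without this the event still cannot be computed uniquely. Which value applies is for the sponsor to decide.

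The cost is wording only. No new data, samples or patients are needed; the sub-therapeutic count moves to a descriptive table. The 10% planning case can then stand as an assumption, with a half-width of 8.3% for 50 patients.

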13. STUDY MONITORING

Apart from the blood samples taken specifically for the study, this research does not alter the participants’ medical care. We have chosen not to establish an independent data safety monitoring board for this study.

14. ACCESS TO DATA AND SOURCE DOCUMENTS

14.1. Access to Data

The sponsor is responsible for obtaining agreement from all parties involved in the study to guarantee direct access to all study sites, source data, source documents, and reports for quality control and audit purposes by the sponsor. Investigators will make available all documents and individual data strictly necessary for monitoring, quality control, and audit of the research to persons with access authorization, in accordance with current legislative and regulatory provisions (Articles L.1121-3 and R.5121-13 of the Public Health Code)

Access to the electronic case report form (e-CRF) will be granted to investigators or clinical research staff (CRAs/technicians) identified in the protocol or delegation log. Each user will have an account in the data capture system with role-based access corresponding to their function. These roles ensure specific access rights. Each user will receive a username and a unique password by email, and passwords will be 8 characters and changed regularly

14.2. Source Data

Any original document or object that proves the existence or accuracy of a data point or fact recorded during the study is considered a source document. Source documents include the patient’s medical records containing the clinical exam notes, any paraclinical exam results (if required), the operative report, postoperative clinical follow-up notes, as well as the data collection sheet filled out in the operating room by the anesthesiologist (this sheet will be filed in the patient’s chart).

14.3. Data Confidentiality

In compliance with current legal provisions (Articles L.1121-3 and R.5121-13 of the Public Health Code), persons with direct access to source data must take all precautions to ensure the confidentiality of information relating to the investigational medicinal products, the research, and the individuals participating in it—particularly regarding the participants’ identities and the study results. These individuals, as well as the investigators themselves, are bound by professional secrecy.

During and after the research, the data collected on participants and transmitted to the sponsor by the investigators (or other specialized collaborators) will be anonymized. Under no circumstances should the names of participating individuals or their addresses be revealed; identifying information will be coded.

Data confidentiality will be maintained by using a coding system for patient information, composed of: the patient’s initials (first letter of last name and first letter of first name(s)) and a 5-digit code number (a two-digit center number followed by a three-digit patient inclusion number from 001 to 999 in chronological order of inclusion)

The sponsor will ensure that each study participant has given written consent for access to their individual data that are strictly necessary for study monitoring, quality control, and audit, as per the legislative and regulatory requirements in force.

15. QUALITY CONTROL AND ASSURANCE

15.1. Instructions for Data Collection

All information required by the protocol must be recorded as it is obtained in the electronic case report form (CRF). Once data entry for a page is completed and data are final, the investigator or person entering the data should mark the page as complete (“lock” the page) so that the data manager can perform data checks for consistency. If a data value cannot be obtained, a specific missing data code (NA or A for not applicable, ND or D for not done, NK or K for not known) should be used to indicate that the data was not collected and cannot be retrieved later (e.g., an assessment done only for research purposes that was not documented in the medical record).

If an entire page of the CRF has all data missing, the investigator or data entry person should mark that page as “Not applicable” in the e-CRF. All access to the study data and any modifications will be logged by the data capture software (Ennov Clinical®).

15.2. Study Monitoring (Site Visits)

Study monitoring will be performed by a clinical research technician. Under the coordination of the lead investigator, this person will be responsible for:

Logistical organization and oversight of the study progress,

Preparing reports on study progress,

Verifying that the CRF is updated (issuing queries for missing information, corrections, etc.),

Handling shipment of blood samples,

Transmitting SAE reports to the sponsor.

The research technician will work according to standardized operating procedures and in collaboration with the clinical research associate (CRA) appointed by the sponsor

15.3. Quality Control

A clinical research associate (CRA) appointed by the sponsor will visit each investigator’s site per a monitoring plan established by the sponsor—at study initiation, periodically during the study (frequency depending on inclusion rate), and at study close-out. During these visits, the following elements will be reviewed: Informed consent documentation, Adherence to the protocol and the defined procedures, Quality of data recorded in the CRF: accuracy, missing data, consistency of data with source documents (medical records, appointment books, original lab results, etc.), Study product management (if applicable).

Each visit will be documented by a monitoring report in writing.

15.4. Data Management

Data collected directly during patient follow-up will be entered once into an electronic case report form by the principal investigator or authorized persons listed on the delegation log, via the web platform (<https://recherche-clinique.chu-amiens.fr/CSOnline/>)

Pre-defined consistency checks in the database will help verify data quality. Queries for correction will be sent to the investigator if inconsistencies are detected

At the end of the study, the database will be locked (frozen) in Ennov Clinical® by a Data Manager from the DRCI of CHU Amiens-Picardie

The centralized data will then be exported and analyzed using SAS® v9.4

The data will subsequently be processed using SAS® v9.4 to perform all statistical analyses as outlined in the “Statistical Aspects” section

15.5. Audit and Inspection

An audit may be conducted at any time by individuals appointed by the sponsor who are independent of the study team. The goal of an audit is to ensure the quality of the study, the validity of its results, and compliance with current laws and regulations

Investigators agree to comply with the sponsor’s requirements and those of regulatory authorities regarding an audit or inspection of the study. An audit can cover all stages of the research, from protocol development to publication of results and archiving of data and documents produced during the study

16. ETHICAL AND REGULATORY CONSIDERATIONS

The sponsor and investigator(s) commit to conducting this research in accordance with the Public Health Code, Good Clinical Practice (ICH GCP E6(R2) of 1996 and the decision of November 24, 2006), and the Declaration of Helsinki (latest version available on the WMA website)

The study will be carried out as described in this protocol. Except in emergency situations requiring specific therapeutic measures, the investigator(s) agree to adhere to the protocol in all respects, particularly concerning informed consent and the notification and follow-up of serious adverse events

CHU Amiens-Picardie, the sponsor of this research, has obtained civil liability insurance for the study with SHAM, in accordance with Article L1121-10 of the Public Health Code

The data recorded during this research will be processed electronically at the Biostatistics Unit of CHU Amiens-Picardie, in compliance with French Data Protection Act No.78-17 of January 6, 1978 (as amended by Law 2004-801 of August 6, 2004) and the EU General Data Protection Regulation (GDPR)

In accordance with the amended Data Protection Act (last modified December 12, 2018) and under GDPR (EU 2016/679) Chapter III “Rights of the Data Subject,” participants have the right to object to data processing, and rights of access, rectification, erasure, and restriction of processing of personal data concerning them

CHU Amiens-Picardie, represented by its current legal representative, is the data controller for this study per GDPR (since it determines the purposes and means of the data processing in this study). Article 9 of the GDPR allows the processing of special categories of personal data, including health data, for research purposes

Participants can exercise their data rights through the Data Protection Officer (DPO) of CHU Amiens-Picardie (email: [contact])

For any complaints regarding the processing of health data, participants may contact the French Data Protection Authority (CNIL) via the website: <https://www.cnil.fr/fr/webform/adresser-une-plainte:content>.

This research falls under the “Reference Methodology” MR-001 pursuant to Article 54, paragraph 5 of the amended Data Protection Act of 6 January 1978. This framework was approved by a decision on January 5, 2006. CHU Amiens-Picardie has signed a compliance commitment to this Reference Methodology.

Protocol Amendments: Any substantial modification—i.e., any change that may significantly affect the protection of participants, the study’s validity, the study results, the quality and safety of the investigational products, the interpretation of supporting scientific documents, or the conduct of the study—must be described in a written amendment submitted to the sponsor. The amendment must obtain a favorable opinion from the CPP and authorization from the ANSM before it can be implemented

Non-substantial modifications (ones without significant impact on any aspect of the study) will be communicated to the CPP for information purposes. All amendments will be approved by the sponsor and by all relevant parties in the study before submission to CPP and ANSM. This approval may require a meeting of the Scientific Committee and/or Safety Committee (if such committees are constituted for the study)

All protocol amendments must be brought to the attention of all investigators participating in the research. The investigators agree to comply with the content of any approved amendments

Any amendment that changes patient management or the benefits, risks, or constraints of the research will require a new patient information sheet and consent form, which must be collected using the same procedure as the initial consent.

